**FIGURE 2 clc23744-fig-0002:**
[figure not shown]
Cardiovascular magnetic resonance imaging protocol. 2ch, two chamber, 3ch, three chamber, 4ch, four chamber, LV, left ventricle, RV, right ventricle

All the image data will be sent to a core‐laboratory located at a dedicated high‐volume and experienced hospital for analysis. Two analysts with at least 5 years working experience in CMR analysis will perform the image analysis independently and blindly to the clinical data or treatment allocation information. Any discrepancy between the two radiologists will be referred to a superior radiologist and cardiologist to adjudicate.

### Baseline and follow‐up examinations

2.6

All patients will be followed for a period of 5 years after PCI (including an in‐patient visit at 6 months, one required out‐patient visit at 30 days and 1 year, and seven another out‐patient or telephone visits). Echocardiography, electrocardiogram, 6‐min walk test and laboratory examinations will be taken at baseline, 6‐month in‐patient visit, and 1‐year out‐patient visit. CMR examinations and life quality evaluations using the Kansas City Cardiomyopathy Questionnaire (KCCQ‐12) will be performed at the acute phase (4–7 days after PCI) and chronic phase (6 months after PCI) respectively. For each visit, patients will be assessed for major adverse cardiac events (MACE) and any medical treatments will be recorded (details in Supporting information A).

### Clinical data collection and monitoring

2.7

All study data will be recorded in a secure electronic data capture system (EDC) designed based on a case record form (CRF) that enables logging of all data entries. For each patient, only the subject number and initials will be recorded in the CRFs. The demographic data, laboratory examination results, PCI procedure records, ECG and echocardiography records will be obtained for each patient by a trained clinical research coordinator. The coordinator will maintain a personal subject identification list to make sure that all records are identified. All investigators will have access to the EDC. The study is monitored by an independent Data and Safety Monitoring Board (DSMB), which will be monitoring the safety of the participants and the interim efficacy analysis. Additionally, an independent Central Endpoint Committee (CEC) will be set up to adjudicate the deaths and important clinical outcomes. The CEC will be rigorously blinded to group allocation of the patients. (Details in Supporting information B).

### Endpoints definition

2.8

The main endpoint is selected to characterize the effect of ARNI on ventricular remodeling as compared to ACEI. Based on the results from previous studies on LV remodeling, change of the indexed LV mass (Δ LVmassi) from baseline to 6‐month follow‐up on CMR is set to be the measurement for the primary outcome.^22^

Similarly, other secondary CMR outcomes include other remodeling parameters from baseline to 6‐month follow‐up (Δ left ventricular ejection fraction [LVEF], Δ LVEDV, Δ LVESV), peak LV strains (global radial peak strain, global circumferential peak strain, and global longitudinal peak strain), strain rates (global radial peak strain rate, global circumferential peak strain rate, and global longitudinal peak strain rate), infarction size as measured through LGE, presence of microvascular obstruction (MVO) on LGE, presence of iron load evaluated on T2* images, T1 mapping, and T2 mapping indexes at the 6‐month CMR.

### The long‐term effects of ARNI on LV remodeling and clinical outcomes in patients will also be assessed in our study

2.9

Thus, key laboratory biomarkers are examined through both arms from baseline to 5‐year follow‐up: (a) HF related laboratory markers (NT‐proBNP, soluble growth stimulating express gene 2 (sST2); (b) myocardium injury related laboratory markers (cardiac troponin T, interleukin [IL]‐1, IL‐6, etc.); (c) MACE, including all deaths (cardiac death vs. non‐cardiac death^23^), non‐fatal myocardial re‐infarction,^24^ hospitalization for worsening heart failure or need for advanced HF therapies (hospital stay >24 h)^25^ (e.g., intravenous use of inotropes, LV assist device placement, or cardiac transplantation) (details in Supporting information C).

The safety assessments for this study include adverse events as follows: incidence of angioedema, symptomatic hypotension, renal insufficiency (i.e., assessed by serum creatinine, estimated glomerular filtration rate [eGFR] and presence of proteinuria, hematuria, and glycosuria), and hyperkalemia. The incidence of the above adverse events will be reported (Supporting information D).

No prespecified sub‐studies are planned in this study.

### Sample size calculation

2.10

The sample size is estimated based on the primary endpoint measurement, that is, Δ LVmassi. Based on the review of published studies and a meta‐analysis summarizing the reported LV remodeling indexes between ARNI group and ACEI group, an average of approximately 4.81 g/m^2^ should be expected for the difference in Δ LVmassi at 6 months from baseline between the ARNI group and ACEI group, with an SD to be 16.65 g/m^2^.^12^ A sample size of 188 patients for each group (i.e., a total of 376 patients) was chosen to achieve ≥80% power for testing superiority of the ARNI group. Considering a maximum of 15% loss to follow‐up (based on the reported follow‐up rate at 4.3%–20%), a target sample size of 442 patients are planned to be initially recruited.^26^, ^27^

### Statistical analysis

2.11

Primary trial analyses will be based on the modified intention to treat (ITT) population in which patients without a measurement of primary outcome will be excluded and additional analyses will also be performed on the per protocol population (PP). Considering that patients who received implantation of implantable cardioverter defibrillator (ICD) or cardiac resynchronization therapy (CRT) within 6 months will be unable to receive the second MRI examination, ITT population will consist of all randomized patients with valid outcome measurement. PP population is a subset of the ITT population in which patients with major protocol deviations will be excluded. Protocol deviations will be defined in the statistical analysis plan.

For the analysis of the primary outcome (change of the indexed LV mass (Δ LVmassi) from baseline to 6‐month follow‐up on CMR), a linear regression model will be employed with treatment as the study variable and baseline measurement of indexed LV mass as a covariate. In addition, adjusted linear model analysis will be performed with the pre‐specified covariates (LVEF, anterior infarction, MVD, presence of MVO on LGE, diabetes, hypertension, and the use of SGLT2i) measured at baseline being added into the above linear model. The crude and adjusted mean differences in the primary outcome together with its 95% confidence intervals at 6‐months will be derived from the linear models. In addition, subgroup analysis of primary endpoint will be performed on the above pre‐specified covariates.

Analysis of secondary continuous outcomes with single follow‐up measurement will be done in a similar fashion as the primary endpoint analysis. Analysis of secondary continuous outcomes with repeated follow‐up measurement will be performed using a linear mixed model with treatment visit, interaction between treatment and visit as fixed effects, the baseline value of the outcome as covariate if it is available, and subject as random effects. The analysis of binary outcomes will also use a generalized linear/mixed model depending on whether there will be a repeated measurement. Odds ratios with their 95% confidence intervals will be derived from the generalized linear/mixed model analysis. For the analysis of time‐to‐event outcome, Kaplan–Meier curves will be presented and compared by log rank test by treatment group, and hazard ratio and its 95% CI will be calculated using Cox regression model with the treatment arm as the study variable.

Missing primary outcome and secondary outcomes with a single measurement will not be imputed but missing secondary outcomes with repeated measurements will be imputed in sensitivity analysis using the last observation carried forward strategy. Missing baseline covariates will be imputed using simple imputation methods in the covariate adjusted analysis based on the covariate distributions in the sample. For a continuous variable, missing values will be imputed from random values from a normal distribution with mean and SD calculated from the available sample. For a categorical variable, missing values will be imputed from random values from a uniform distribution with probabilities *P*
_
*1*
_, *P*
_
*2*
_,…, and *P*
_
*k*
_ from the sample. Seed for the imputation is set as the date of data analysis (e.g., 270 521).

The study is powered to make a single comparison in the primary outcome at 6 months only and other comparisons are exploratory in nature. Therefore, there is no multiplicity issue. All analyses will be described in detail in the statistical analysis plan. SAS 9.4 will be employed for the statistical analyses.

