### Study design

2.1

This study is an investigator‐initiated, multi‐center, open‐label, parallel‐group, superiority study (Figure 1). Patients will be recruited from approximately 20 hospitals in China. This study has been approved by the ethic committee of West China hospital and all participating centers. PERI‐STEMI is registered at ClinicalTrials.gov (NCT04912167).

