### Randomization and binding procedure

2.3

No run‐in period is included for PERI‐STEMI. Following screening patients who fulfill the eligibility criteria will be randomized (1:1) to either sacubitril–valsartan or enalapril. Permuted block randomization stratified by center will be employed. Randomization will be performed through an Interactive Web‐based Response System, for which a random allocation sequence is created using a standard computerized random‐number generator. This study is an open‐label trial, but the radiologists responsible for imaging analysis will be rigorously blind to the clinical and allocation information.

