### Imaging study and analysis

2.5

Image acquisition will be performed twice by qualified cardiac MRI experts with over 5 years working experience of cardiac MR imaging. The participating centers need to be equipped with MRI scan on 1.5 T or 3.0 T platforms with dedicated cardiac receiver coils. During imaging, the patients will be kept in supine position. A standard electrocardiographic triggering device will be used for heart rate triggering and monitoring.

A sample protocol is provided for all modalities (Figure 2). The participating sites will be allowed to use their own acquisition protocols, provided that standard cine, late gadolinium enhancement (LGE) and mapping images should be acquired according to the current practice guidelines. In the sample protocol, a balanced steady state free precession sequence (bSSFP) will be used to acquire continuous short‐axis (SAX) slices encompassing the whole LV, standard two‐, three‐, and four‐chamber cine images during repeated breath holds. After then, a dose of 0.1 mmol/kg Gadolinium will be injected at a flow rate of 2.5–3.0 ml/s. LGE images will be acquired 10–15 min after contrast administration using a phase‐sensitive inversion recovery sequence. Pre‐contrast T1 mapping and T2 mapping will be acquired, and a repeat MOLLI T1 mapping will be performed after LGE for the post‐T1 mapping.

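### Centre is the only stratification factor named but is in neither the primary nor the adjusted model; adding it is a small, nearly free gain in precision

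*Protocol article*

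**What the plan says.** On allocation, section 2.3 (Randomization and binding procedure) states: "Permuted block randomization stratified by center will be employed". It names no other stratification factor. Section 2.1 (Study design) gives the number of centres: "Patients will be recruited from approximately 20 hospitals in China".

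On analysis, section 2.11 (Statistical analysis) fixes two models for the change in indexed LV mass at 6 months:

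- Primary model: "a linear regression model will be employed with treatment as the study variable and baseline measurement of indexed LV mass as a covariate".
- Adjusted model: the same, plus "LVEF, anterior infarction, MVD, presence of MVO on LGE, diabetes, hypertension, and the use of SGLT2i".

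Centre is in neither. The same section analyses single-measurement secondary continuous outcomes in the same way. For repeated measurements it uses a mixed model whose only random effect is the subject.

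On imaging, section 2.5 (Imaging study and analysis) allows "MRI scan on 1.5 T or 3.0 T platforms with dedicated cardiac receiver coils" and adds: "The participating sites will be allowed to use their own acquisition protocols". All images go to one core laboratory for blinded reading.

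**The concern.** Stratifying by centre balances the arms within each centre, so differences between centres largely drop out of the treatment comparison. A model without centre does not know this. It leaves the between-centre variance in the residual and reports a standard error larger than the true sampling error of the estimate. The confidence interval is then wider than the design warrants, and the test rejects less often than its nominal level.

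What is at stake is precision that the randomisation has already secured. The article names the covariates of both models, so this is a comment on a stated model and not on something left for the statistical analysis plan.

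**Working it through.** **Inputs from the article.** Section 2.10 (Sample size calculation) gives the effect as "an average of approximately 4.81 g/m^2^ should be expected for the difference in" the change in indexed LV mass, "with an SD to be 16.65 g/m^2". It plans 188 patients per group (376 in total) for at least 80% power, and 442 recruited to allow for 15% loss. Allocation is 1:1. Alpha is not stated; two-sided 0.05 is assumed, in line with the 95% confidence intervals.

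**The plan's own figure.** n per group = 2 × [16.65 × (1.960 + 0.842) / 4.81]² = 188.09, which rounds up to 189. Power at 188 per group is 79.98%, and 376 / 0.85 = 442.4. The stated sample size therefore reproduces up to rounding. One-sided 0.05 gives 149 per group and does not.

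**Assumptions for the check.** Let ρ be the share of the residual variance explained by centre. The documents give no value, so a range is shown. The SD of 16.65 is taken as the total residual SD, centre included. The formulas assume exact balance within centres and ignore the degrees of freedom used by centre.

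**Formulas.**

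- Model SE without centre: 16.65 × √(2/188) = 1.717, so z = 4.81 / 1.717 = 2.80.
- True SE: 1.717 × √(1 − ρ). The model SE is too large by the factor 1/√(1 − ρ).
- Type I error without centre: 2 × [1 − Φ(1.96/√(1 − ρ))].
- Power without centre: Φ((z − 1.96)/√(1 − ρ)).
- Power with centre: Φ(z/√(1 − ρ) − 1.96).

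| ρ (assumed) | True SE | SE too wide by | Type I error without centre | Power without centre | Power with centre |
|---|---|---|---|---|---|
| 0.02 | 1.700 | 1.0% | 4.8% | 80.2% | 80.8% |
| 0.05 | 1.674 | 2.6% | 4.4% | 80.6% | 82.0% |
| 0.10 | 1.629 | 5.4% | 3.9% | 81.2% | 84.0% |
| 0.20 | 1.536 | 11.8% | 2.8% | 82.6% | 87.9% |

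Worked line for ρ = 0.05: √0.95 = 0.9747. Power without centre is Φ(0.841/0.9747) = Φ(0.863) = 80.6%. Power with centre is Φ(2.801/0.9747 − 1.960) = Φ(0.914) = 82.0%.

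**Simulation without the exact-balance assumption.** Settings: 442 randomised, 20 centres of unequal size, blocks of 4 (assumed), 15% random loss, centre as a fixed effect, 4,000 runs per setting. The Monte Carlo standard error of each power is about √(0.8 × 0.2/4000) = 0.6 points.

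| ρ | Power without centre | Power with centre | Gain (points) |
|---|---|---|---|
| 0.02 | 80.13% | 80.08% | about 0 |
| 0.05 | 80.83% | 81.65% | 0.8 |
| 0.10 | 80.88% | 83.33% | 2.5 |
| 0.20 | 80.30% | 85.88% | 5.6 |

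At ρ = 0.10 the simulated type I error is 4.0% without centre and 5.0% with it. At ρ = 0 the mean SE is 1.72 without centre and 1.73 with it, which is the price of including centre when it explains nothing.

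**The case against.** The strongest reply is that little is at risk. Power without centre stays at about 80% or just above for every share examined, so the sample size goal is met. The loss exists only against an analysis that the sample size never assumed. The error is in the conservative direction. All of this stands.

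The second reply concerns the centre share. A reader might infer from the mixed field strengths and local acquisition protocols that it must be large. The documents do not support that. The endpoint is a change within the patient, adjusted for baseline, and a constant scanner offset largely cancels if both scans are done the same way. Reading at one core laboratory limits differences between readers at different sites. The article does not say whether a patient's two scans use the same scanner. A condensed article commonly leaves that to the full protocol, so its absence is no finding.

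A reader might also cite the mention of regional variation in section 4.1 (Limitations). That sentence says only that variation might occur, and it concerns clinical outcomes, not LV mass on CMR. Likewise, one might expect T1 and T2 mapping to suffer more, but the documents give no figure from which to compute this, and those outcomes are declared exploratory.

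Third, the handling of centre could appear in the statistical analysis plan, to which section 2.11 refers for detail. This carries limited weight, because the article already lists the terms of both models and centre is not among them.

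**Conclusion.** The point holds as a modest one. The only stratification factor named is absent from the primary and adjusted models. If centre carries part of the residual variance, the intervals are slightly too wide and the test is slightly conservative. For assumed shares of 2% to 10%, the power forgone is about 0.5 to 2.7 points by formula and about 0 to 2.5 points by simulation. A 20% share would raise this to between 5 and 6 points, but nothing in the documents points to a share of that size.

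A reader might infer that the trial is underpowered, or that its result would be biased or falsely positive. None of these follows: the estimate is unbiased, the type I error is not inflated, and planned power is intact. The power figures rest on the assumed share, on 16.65 as the total residual SD and on two-sided 0.05. This is a small efficiency gain at almost no cost, not a defect that threatens the conclusion.

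**What to change.** Add centre to the primary model, the adjusted model and the models for secondary continuous outcomes. Use either a random intercept for centre, or fixed centre effects with a rule for pooling small centres that is written down before unblinding. State the choice in the statistical analysis plan and note it as a change from the published model.

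The cost is one term per model. With 376 evaluable patients the primary model has 376 − 3 = 373 residual degrees of freedom. Fixed effects for 20 centres use 19 of them and leave 354. A random intercept adds one variance parameter. Sample size and data collection do not change.

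### The leading model for the primary outcome leaves out seven pre-specified baseline covariates, which forgoes precision, and no sentence names the model that decides superiority

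*Protocol article*

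**What the plan says.** The protocol article, section 2.11 (Statistical analysis), describes two linear models for the change in indexed LV mass from baseline to 6 months.

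- The first contains treatment and baseline indexed LV mass.
- The second is introduced with "In addition, adjusted linear model analysis will be performed with the" pre-specified covariates. It adds LVEF, anterior infarction, multivessel disease (MVD), microvascular obstruction (MVO), diabetes, hypertension and SGLT2 inhibitor use, all described as measured at baseline.

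Both are reported: "The crude and adjusted mean differences in the primary outcome together with its 95% confidence intervals" are to come from these models. The section ends by stating that "The study is powered to make a single comparison in the primary outcome at 6 months only". It treats other comparisons as exploratory and concludes that multiplicity does not arise.

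For the covariate-adjusted analysis, a missing covariate is replaced by one random draw from a distribution fitted to the observed values. The seed is the date of the data analysis.

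Section 2.10 (Sample size calculation) gives the design inputs: "an average of approximately 4.81 g/m^2^ should be expected for the difference in" the change between arms, "with an SD to be 16.65 g/m^2". The evaluable number, 188 per arm and 376 overall, "was chosen to achieve ≥80% power for testing superiority of the ARNI group".

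**The concern.** In a linear model for a randomised comparison, baseline covariates that predict the outcome leave the target mean difference unchanged and shrink its standard error. The trial already names seven such candidates, collects them and has a rule for filling them in, yet keeps them out of the leading model. If they are predictive, the less precise estimate has been put in front.

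The second issue is a missing label. Two estimates of the same primary effect appear side by side, each with a 95% interval. The statement that only one comparison is made is true only if one of them decides. If they fell on opposite sides of the 5% threshold, a reader would have to infer from the order of the sentences which is the trial's answer.

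**Working it through.** **Inputs**

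- From section 2.10: difference δ = 4.81 g/m², SD σ = 16.65 g/m², n = 188 per arm.
- Two-sided α = 0.05 is assumed. The article does not state it, but it matches the 95% intervals and reproduces the sample size; one-sided 0.05 gives 149 per arm and does not.
- R² is the share of the remaining outcome variance explained by the added covariates. The document gives no value, so 0, 0.05, 0.10 and 0.20 are assumed.
- The article does not say whether 16.65 is a raw SD of change or a residual SD after baseline adjustment. It is taken here as the residual SD before the extra covariates are added.

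**Step 1: the plan's own figure.** n = 2 × [σ(1.960 + 0.842)/δ]² = 2 × [16.65 × 2.802/4.81]² = 188.1 per arm, against 188 stated. Power at 188 per arm is 79.98% by the normal approximation and 79.8% by the noncentral t. The sample size therefore rests on a plain comparison of two means, claims no gain from covariates, and has almost no margin at 376 evaluable patients. The recruitment target also follows: "Considering a maximum of 15% loss to" follow-up gives 376/0.85 = 442.4, against 442 stated.

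**Step 2: adding covariates.** Replace σ by σ√(1 − R²). The standard error is σ√(1 − R²) × √(2/188). The equivalent evaluable total without the extra covariates is 376/(1 − R²). Power is by noncentral t.

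| Assumed extra R² | SD | Standard error | 95% half-width | Power | Equivalent total |
|---|---|---|---|---|---|
| 0 | 16.65 | 1.717 | 3.37 | 79.8% | 376 |
| 0.05 | 16.23 | 1.674 | 3.28 | 81.8% | 396 |
| 0.10 | 15.80 | 1.629 | 3.19 | 83.8% | 418 |
| 0.20 | 14.89 | 1.536 | 3.01 | 87.8% | 470 |

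The lost degrees of freedom hardly matter. With seven added covariates, 376 − 2 − 8 = 366 remain (two arms, baseline LV mass and the seven), and the power figures move by no more than about 0.1 point.

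**Step 3: how often the two models would disagree.** Under the planned effect, the two test statistics are taken as bivariate normal with correlation √(1 − R²). They fall on opposite sides of 5% in about 5%, 7% and 11% of trials at R² of 0.05, 0.10 and 0.20.

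**Step 4: which covariates are safely pre-treatment.** Anterior infarction, MVD, diabetes and hypertension describe the presenting infarct, the coronary anatomy or the history. MVO is read from late gadolinium enhancement on the baseline CMR, which the Abstract and section 2.6 place 4–7 days after PCI. The article does not place that scan before randomisation or first dose. The same doubt covers LVEF if it is read from CMR, and SGLT2 inhibitor use, which section 2.4 leaves to the physician during care. Baseline LV mass comes from the same scan, so the timing needs confirming whichever model leads.

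**The case against.** The strongest reply is that the hierarchy is already visible. One model is given for the primary outcome, the other follows under "In addition, adjusted linear model analysis will be performed with the" extra covariates, and the closing paragraph speaks of a single powered comparison. Adjusting for the baseline value of the outcome, with a fuller model as support, is accepted practice. An explicit label may also stand in the statistical analysis plan, which is not shown. Much of this stands: the text points to the smaller model as deciding, and what is lacking is a label. The choice of leading model, however, is made in this document, and on that reading the precision point applies in full.

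Three further objections limit the point.

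- The document calls the covariates pre-specified, not prognostic, and its Discussion says LVEF is not an ideal predictor of adverse remodelling. The gain could be small or nil.
- If 16.65 is a raw SD, baseline LV mass may already lift power above 79.8%, and the margin is then larger than it looks.
- Moving all seven covariates into the deciding model without checks would bring in variables of uncertain timing and an imputation that depends on the analysis date. The fix has to deal with both.

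A reader might infer that the plan inflates its type I error. Claiming success if either model were significant would give about 6.0%, 6.5% or 7.1% at R² of 0.05, 0.10 or 0.20, but the plan states no such rule. A reader might also infer that the trial is underpowered because of its model. It is not, since the sample size assumes no covariate gain.

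**Conclusion.** The point holds as a matter of efficiency and labelling. The leading model omits covariates that are already named and collected, and the article implies but does not state which estimate decides. What is forgone is about 2, 4 or 8 percentage points of power at an assumed extra R² of 0.05, 0.10 or 0.20, and nothing at 0. This rests on two-sided 5%, 188 evaluable patients per arm, and 16.65 as the residual SD before the added covariates. The document supports neither a contradiction, nor an error rate above 5%, nor a shortfall from the planned power. The change is worth making because it is cheap and the design has little margin.

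**What to change.** In section 2.11, and in the statistical analysis plan to match:

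1. State that superiority is decided by one linear model for change in indexed LV mass, with treatment, baseline indexed LV mass, anterior infarction, MVD, diabetes and hypertension. Add LVEF, MVO and SGLT2 inhibitor use only if each is confirmed as recorded before randomisation or first dose.
2. Label the model with baseline LV mass alone as a sensitivity analysis that does not decide.
3. For missing covariates in the deciding model, replace the single random draw seeded by the analysis date with a fixed, pre-stated and reproducible rule applied without regard to arm, for example mean imputation for continuous covariates and a missing category for categorical ones.

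The cost is wording before unblinding, with no new data or patients. The downsides are a few degrees of freedom out of more than 360, and a primary result that depends to some extent on imputed covariates. If the sponsor prefers to keep the smaller model as deciding, one sentence saying so would settle the labelling, but the precision would still be forgone.

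### Laboratory biomarkers are defined as 5-year outcomes but scheduled only to 1 year; separately, last observation carried forward is a poor sensitivity analysis for repeated outcomes after infarction

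*Protocol article*

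**What the plan says.** All references are to the protocol article.

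- **Outcome definition (section 2.9).** "key laboratory biomarkers are examined through both arms from baseline to 5‐year follow‐up". The list that follows names NT-proBNP and sST2, then troponin T and interleukins, and then MACE as item (c).
- **Visit schedule (section 2.6).** Follow-up lasts 5 years: "All patients will be followed for a period of 5 years after PCI". For blood tests, "laboratory examinations will be taken at baseline, 6‐month in‐patient visit, and 1‐year out‐patient visit". Beyond the 30-day, 6-month and 1-year visits there are "seven another out‐patient or telephone visits", and no laboratory test is listed at any of them. The section refers to Supporting information A for detail.
- **Main analysis (section 2.11).** "Analysis of secondary continuous outcomes with repeated follow‐up measurement will be performed using a linear mixed model". Treatment, visit and their interaction are fixed effects, and the baseline value is a covariate where available. No imputation of the outcome is stated for this model.
- **Missing data (section 2.11).** "missing secondary outcomes with repeated measurements will be imputed in sensitivity analysis using the last observation carried forward strategy". The primary outcome is not imputed, and every comparison other than the primary one is called exploratory.

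**The concern.** There are two separate faults.

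The first is a contradiction about when biomarkers are measured. If 5-year values are intended and sites work from section 2.6, the samples will not be drawn and cannot be recovered later. If only 1-year values are intended, section 2.9 promises an outcome that the trial will not have.

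The second is the named robustness check. LOCF assumes that a patient's value stays where it was at the last sample. Baseline here follows an acute infarction, and section 2.9 itself groups some of these markers as indicators of myocardial injury, so a fall is expected. The same rule covers echocardiography and the 6-minute walk, which also have two follow-up measurements. The Discussion undercuts the no-change assumption for these: it describes stunning as common, and it notes that some patients with a low ejection fraction in the acute phase recover later. A sensitivity analysis should vary the assumption that the main model makes about unseen values. LOCF instead substitutes a different and less plausible assumption, and counts the filled values as data. Agreement or disagreement with the mixed model would then be hard to interpret.

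**Working it through.** **1. Schedule against outcome definition.**

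| | Section 2.9 | Section 2.6 |
|---|---|---|
| Last biomarker time point | 5 years = month 60 | 1 year = month 12 |

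Months of the stated period after the last scheduled test: 60 − 12 = 48. As a share: 48/60 = 80%. A telephone visit yields no blood sample, and the out-patient alternative has no laboratory test listed.

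**2. What LOCF can do to a treatment difference (illustration).** The article gives no missingness rate for biomarkers. The only loss figures are in section 2.10: a planned maximum of 15% and a reported range of 4.3% to 20%, both given for the primary-endpoint sample size. The 15% reproduces the plan's own inflation: 376/0.85 = 442.4, against 442 stated. Using these figures for biomarkers is an assumption.

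Suppose a share *d* in each arm has only a baseline value, that value is carried forward, and loss is unrelated to outcome. Those patients contribute a change of zero. With a true between-arm difference in change of Δ,

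expected LOCF difference = (1 − *d*) × Δ + *d* × 0 = (1 − *d*) × Δ.

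| *d* | Factor 1 − *d* |
|---|---|
| 4.3% | 0.957 |
| 15% | 0.85 |
| 20% | 0.80 |

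**3. Unequal loss.** Let both arms share the same true change *C* (no treatment effect), with loss *d*₁ and *d*₂. The LOCF mean changes are (1 − *d*₁)*C* and (1 − *d*₂)*C*, so the spurious difference is (*d*₂ − *d*₁)*C* in absolute size.

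- 10% v 15%: 5% of *C*.
- 10% v 20%: 10% of *C*.

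These loss pairs are assumed. Equal loss pulls the estimate towards no difference, while unequal loss can push it either way, depending on which arm loses more. The direction of the LOCF error is therefore not fixed in advance.

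**The case against.** **The schedule conflict may be loose drafting.** Supporting information A is not shown and could list later tests, and the 5-year phrase heads a list that includes MACE, which is collected at every visit. Both points are fair. However, the grammatical subject of the section 2.9 sentence is the laboratory biomarkers. On the first reading section 2.6 is wrong, and on the second section 2.9 is wrong. The text needs correcting either way.

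**LOCF is confined to a sensitivity analysis.** A reader might infer that gaps will be filled by LOCF in the main results. The text does not support that: the main analysis is the mixed model.

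**The two faults do not combine.** A reader might also infer that 1-year values would be carried forward to stand in for year 5. The article does not say so. Section 2.11 imputes missing outcomes, and a sample that was never scheduled is not ordinarily a missing one.

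**The size is conditional.** It is tempting to say that LOCF will shrink differences by 15% and understate the standard error by about 8%, from √(376/442) = 0.922. That would need every patient lost at the planned maximum rate to have only a baseline value, and that value to be the one carried forward. A patient missing only the 1-year sample would carry the 6-month value. Baseline enters the model as a covariate, so carrying only post-baseline values is an equally open reading, under which the shrinkage worked out above does not arise. On the same figures, 0.85/0.922 = 0.92, so the test statistic would fall by about 8%, which for a superiority comparison is conservative. These figures are not a forecast.

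**Low stakes.** The outcomes are exploratory, and no sample size, power or primary conclusion changes. This stands and limits the severity.

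**Conclusion.** The point holds in two parts.

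- **Contradiction.** As printed, the biomarker outcome runs to month 60 and its last scheduled measurement is at month 12. The 5-year outcome cannot be obtained from the published schedule. This rests on the article's text alone, and an unseen supplement could only show which section is at fault.
- **Sensitivity method.** LOCF suits repeated outcomes after acute infarction badly and does not test the mixed model's missing-data assumption in a defined direction. Its possible effect on a between-arm difference is a factor of 0.957 to 0.80. That range assumes that baseline values are carried forward, that loss is equal across arms and unrelated to outcome, and that the loss range from section 2.10 applies to biomarkers. Whether LOCF is more biased than the mixed model in practice depends on why values are missing, so no general ranking is claimed.

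The main mixed-model analysis and the primary endpoint are untouched. The correction is minor to moderate.

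**What to change.** 1. **Reconcile sections 2.6 and 2.9.** Either restate the biomarker horizon as baseline to 1 year, or correct the schedule if later samples are intended. Separate MACE from the biomarker list so that its 5-year follow-up stands on its own.
2. **Limit the repeated-measures analysis to scheduled visits.** State that no value is imputed at a visit where the measurement was not planned.
3. **Replace LOCF.** Use multiple imputation consistent with the specified mixed model, then add delta (tipping-point) shifts to the imputed values separately by arm. A shift of zero corresponds to the mixed model's own assumption, and the other shifts show how far the estimate moves under stated departures from it. Fix the range of shifts in the statistical analysis plan before outcome data are examined by arm.

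The cost is protocol and analysis-plan wording and slightly more programming. Restating the horizon gives up a 5-year biomarker claim that the printed schedule cannot support, while keeping that claim means adding later samples to the schedule.
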